## Abstract

**Background:**

The current surgical treatment for patients diagnosed with progressive and severe adolescent idiopathic scoliosis (AIS) consists of the correction of the spinal curvature, followed by posterior spinal fusion (PSF). However, research has uncovered short- and long-term complications of posterior spinal fusion in patients with AIS. Minimally invasive growing rod techniques have successfully been used to treat patients with early-onset scoliosis and neuromuscular scoliosis. It may be questioned if minimally invasive posterior spinal nonfusion (PSnF) surgery with bipolar instrumentation can be used for the treatment of AIS.

**Objective:**

This study will be performed to monitor the efficacy and safety of PSnF surgery by using a commercially available Conformité Européenne-certified spinal implant consisting of bilateral bipolar one-way self-expanding rods (OWSER) for the treatment of patients diagnosed with AIS.

**Methods:**

In 14 selected patients with AIS with Lenke 1-6 curves, minimally invasive PSnF surgery with the OWSER system is performed after the failure of conservative treatment (curve progression of >5° within 1 year). The patients are over 7 years of age, with a major Cobb angle of ≥30°, sufficient flexibility, and a Risser stage of ≤2. Patients will be followed over time, according to the standard medical care. Efficacy will be measured using radiological and patient satisfaction assessments and safety will be determined by the amount of perioperative complications.

**Results:**

Patient inclusion started on November 17, 2021 and we hope to finalize patient inclusion by the beginning of 2025. The first results will be expected by the beginning of 2024.

**Conclusions:**

Minimally invasive PSnF in patients with AIS is presented as a less invasive surgical technique that prevents the progression of the scoliotic curve and that allows minor posture correction of coronal imbalance. This will be the first study to examine whether the PSnF bipolar OWSER instrumentation will be the next generation of surgical instrumentation in AIS.

**Trial Registration:**

ClinicalTrials.gov NCT04441411; https://clinicaltrials.gov/study/NCT04441411

**International Registered Report Identifier (IRRID):**

DERR1-10.2196/47222

## Introduction

Adolescent idiopathic scoliosis (AIS) is a 3D deformity of the spine that is clearly associated with the adolescent growth spurt [1]. Up to 10% of patients diagnosed with AIS require some form of treatment, and almost 0.3% will eventually undergo corrective spinal surgery [2]. When the scoliotic curve exceeds 40° to 45°, surgical correction followed by posterior spinal fusion (PSF) is regarded as the standard surgical treatment for AIS [3,4].

Both short- and long-term complications of PSF have been described in relation to AIS, such as spinal imbalance, implant failure, infection and wound complications, degenerative disk disease (16%), postoperative pain, distal adding-on, and proximal junctional kyphosis [5-10]. These complications all result in additional treatment or possibly a reduced quality of life. Therefore, there is a need for a type of minimally invasive spinal surgery that allows natural growth, enables spontaneous spinal balance correction and prevents full spinal fusion to improve the outcomes of patients with AIS.

Minimally invasive nonfusion spinal surgery in AIS is not new. Anterior vertebral body tethering and a concave distraction technique (ApiFix) have been used as nonfusion techniques in patients with AIS, although with mixed results and high complication rates [11-13]. In spinal deformity surgery, nonfusion techniques with growing rods have been used for patients diagnosed with progressive early-onset scoliosis (EOS) or neuromuscular scoliosis (NMS) [14-16]. The rods function as an “internal brace” of the spine and aim to control or reduce spinal deformity. These minimally invasive nonfusion surgical techniques have been developed to limit the progression of the curve and to improve the thoracic volume while allowing the spine and thorax to grow along with the natural growth of the patient [17].

### Proposed Surgical Technique

The surgical treatment described in this protocol is the standard treatment protocol for scoliosis surgery, including perioperative antibiotic prophylaxis, a supine position on the spine table, and intraoperative motor-evoked potential (MEP) and somatosensory-evoked potential (SSEP) monitoring. Traction is applied to the patient’s head using a Mayfield skull clamp, and distal traction (10% to 15% of body weight) is applied with boots on the legs to achieve intraoperative correction. The level of instrumentation is determined according to the principles developed by Lenke [18,19].

A total of 2 short 5-10–cm midline incisions are placed over the high thoracic and thoracolumbar anchor points. In the high thoracic region, 4 pedicle screws are placed. Additionally, 2 transverse process hooks are placed at the upper-level vertebra to prevent proximal junction kyphosis. At the thoracolumbar anchor region, 4 pedicle screws are placed, including a short rod on both sides (Figure 1).

**Figure 1 figure1:**
[figure not shown]
Example of NEMOST growing domino and E-SPINE system construct.

The one-way self-expanding rods (OWSERs) and domino is a CE-marked commercially available form of instrumentation registered as a NEMOST rod (E-SPINE, Euros; corresponding certificate: N°CE639319; Figure 2).

**Figure 2 figure2:**
[figure not shown]
The one-way self-expanding rod (OWSER) and domino registered as NEMOST rod.

The OWSER is inserted into the subfascial plane between the 2 incisions from the caudal to the cranial region, guided by a cranio-caudal introduced chest tube under the superficial fascia. Subsequently, the OWSERs are fixed to the cranial anchors with an additional cross connector between the 2 rods. After the insertion of the rod, a moderate concave distraction is performed before the OWSER is connected to the laterally positioned small smooth thoracolumbar rods.

The initial correction of the scoliotic curve is obtained via intraoperative traction. The sagittal plane correction is obtained as a result of kyphotic rod contouring before rod insertion. The notched ratchet part of the rod, including the temporarily fixed domino connector that is positioned downward, remains straight to allow future elongation. The one-way self-expanding domino connector slides passively and gradually (1-mm step ratchet) along the notched part of the long rod. Rotation of the rod in the domino connector is prevented by a flat part of the notched rod (Figure 2). Postoperatively, patients have unrestricted mobilization during normal daily activities. Patients have follow-up appointments that adhere to the standard protocol of postoperative scoliosis care (Table 1).

**Table 1 table1:** Scheme used during clinical care in children treated with nonfusion one-way self-expanding rods.

	Screening (1-2 months preoperative)	30 days preoperative	Preoperative	Postoperative clinic	2 months post surgery	Every 6 months postoperative till 2 years after skeletal maturity
Explanation providing informed consent	✓					
Sign informed consent		✓				
Examination treating MD		✓			✓	✓
X-rays	✓		✓	✓	✓	✓
Clinical picture spine (standing position)		✓				✓
SRS^a^ questionnaire		✓			✓	✓

^a^SRS: Scoliosis Research Society.

The minimally invasive nature of the procedure, combined with the system’s ability to allow the patient’s natural growth while working as an internal brace, holds promise for improvement in the treatment of progressive AIS. This aligns with earlier results that have been shown for patients with NMS and EOS [14,20].

To the best of our knowledge, a minimally invasive posterior spinal nonfusion (PSnF) surgery with OWSER has not previously been used in patients with AIS.

This study describes a study protocol for a clinical trial. This study aims to evaluate the efficacy and safety of a nonfusion bipolar self-expanding rod system, here referred to as the “nonfusion OWSER system,” in the surgical treatment of patients with progressive AIS. Based on the positive surgical results and relatively low complication rates found when this type of system is used in patients with NMS or EOS [14,16,20], we hypothesize that the minimally invasive surgery using the nonfusion one-way self-expanding rod system (nonfusion OWSER) system is safe and efficient for the surgical correction of progressive AIS.

## Methods

### Ethical Considerations

The study protocol (version 3, October 29, 2021) describes a single-center cohort study. Ethics approval was granted by the Medical Ethical Committee of the Amsterdam University Medical Center (UMC) in the Netherlands, on May 20, 2020 (METC 2020_023, NL67124.018.19). Due to the COVID-19 pandemic, we were unsure if the study would be able to continue. This has led to a delay in the publication of this study protocol. This study will be conducted according to the principles of the Declaration of Helsinki (2013) and in accordance with the Medical Research Involving Human Subjects Act (WMO). It is registered in the Dutch trial register (NL8659) and the international trial register (NCT04441411). On October 14, 2023, a total of 5 patients have been included in the prospective study.

### Participants

All patients will be recruited by 1 single surgeon embedded in a multidisciplinary scoliosis team in the Amsterdam UMC in the Netherlands. Both patients and patients’ legal guardians must sign an informed consent form before the patient is included in the study. The inclusion criteria are (1) a diagnosis of AIS, (2) an age of >7 years, (3) a primary Cobb of >30°, (4) failed nonoperative treatment, (5) a Risser grade of ≤2 and a skeletal age of hand and wrist x-rays of ≤14 years, (6) a nonrigid curve, (7) all Lenke types, and (8) no previous spinal surgery.

A patient who meets any of the following criteria will be excluded from participation in this study: (1) nonidiopathic scoliosis: musculoskeletal or neurologic conditions responsible for the cause of the spine curvature (ie, neuromuscular, congenital, or syndromic scoliosis); (2) history of previous spine surgery; (3) Risser grade >2; (3) disease or deformity likely to affect the stability of the device (ie, inadequate anatomy of pedicles, trauma or tumor in fixation region, severe osteoporosis, bone destruction, or poor bone quality); (4) nonreducible scoliosis; (5) known allergy or intolerance to one of the device material; (6) acute or chronic infections, local or systemic; (7) absence or insufficiency of covering tissues; or (8) pathological obesity.

### Data Collection and Statistical Analyses

Data will be collected at baseline, directly post surgery, after 2 months, and every 6 months after the operation until 2 years after skeletal maturity (see Table 1).

To describe the included patient group, patient characteristics such as age at surgery, sex, height, weight, medical and surgical history, blood loss during surgery, operative time, length of hospitalization, upper and lower level of fixation, short- and long-term complications (surgical site infections, neurological complications, implant failure, proximal junctional kyphosis, etc), and when applicable, secondary surgery (including the time between the first and second surgery) will be extracted from the patient's medical record. The data will be summarized in tables listing the mean, SD, median, minimum, maximum, and number of subjects for continuous data or in tables listing the quantities and percentages for categorical data, where appropriate.

For the primary goal, to analyze the efficacy of OWSER, the correction of the scoliotic curve will be measured by comparing the preoperative and postoperative Cobb angle with the Cobb angle 2 years after maturity. Radiological parameters will be measured by an orthopedic resident, trained to measure all radiological parameters. Measurements will be randomly verified by a senior experienced spine surgeon. Measured radiological parameters include the main Cobb angle (measured as defined by Cobb [21]), compensatory Cobb angle, correction after surgery, sagittal balance (thoracic kyphosis, lumbar lordosis, and proximal and distal junctional angle), pelvic parameters (pelvic obliquity, sacral slope, pelvic incidence, and pelvic tilt), Risser sign, and vertebral rotation based on full spine standing posterior-anterior and lateral radiographs. Differences between the Cobb angles and growth will be analyzed using repeated ANOVA measures. To correct for possible confounders, a mixed-model regression analysis will be performed including age at surgery, Risser sign, weight, and sex.

Patient satisfaction and function will be assessed using patient appearance (shoulder imbalance and pelvic imbalance) and patient-reported outcome measurements using the Scoliosis Research Society's-22r (SRS-22r) questionnaire. This questionnaire is provided in Dutch and the use of the questionnaire has previously been validated [22]. The safety of the surgical device will be monitored and registered based on (serious) adverse events and complication rates. Radiological and patient-related outcomes will be used to assess the clinical outcomes and with this, the efficiency of the implant. These parameters will be measured at every follow-up moment (Table 1).

In case of missing values at the follow-up, the patient will remain included in the study. Based on the amount of missing values, the patients will be excluded from the calculations from the specific follow-up moment. This will be described in the results section of the specific study. A *P* value of <.05 will be regarded as statistically significant.

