### Adverse Events

Adverse events (AEs) and serious adverse events (SAEs) are documented according to the definition of the Dutch Ethics Committee and will be acted on accordingly. AEs are defined as any undesirable experience occurring to a subject during the study, whether or not considered related to the investigational product. These will be actively reported by the subject or observed by the investigator or his staff. All AEs will be recorded throughout the study, and their severity and relation to the investigational device will be determined.

SAEs are documented as any untoward medical occurrences or effects that result in death, are life-threatening (at the time of the event), require hospitalization or the prolongation of existing inpatients’ hospitalization, in persistent or significant disability or incapacity, are congenital anomalies or birth defects, or involve any other important medical events that did not result in any of the outcomes listed above due to medical or surgical interventions but that could have been based upon appropriate judgment by the investigator.

The research and treatment team must report any SAEs via telephone or email correspondence within 24 hours after the occurrence of the event to the principal investigator and the delegated medical board of directors. A completed initial SAE report must be sent, as indicated in the study’s case report form.

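### Proximal junctional kyphosis is taken as a complication from the medical record, although the junctional angles measured at every follow-up could classify it and are not linked to the safety rate

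*Protocol article*

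**What the plan says.** All of the relevant text is in the protocol article.

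- **Complications.** Data Collection and Statistical Analyses opens its descriptive paragraph with "To describe the included patient group, patient characteristics such as age at surgery". The list that follows includes "short- and long-term complications (surgical site infections, neurological complications, implant failure, proximal junctional kyphosis, etc", and the sentence closes by saying that these items "will be extracted from the patient's medical record".
- **Junctional angles.** The next paragraph of that section lists the radiological parameters, among them "sagittal balance (thoracic kyphosis, lumbar lordosis, and proximal and distal junctional angle". On the reader it says: "Radiological parameters will be measured by an orthopedic resident, trained to measure all radiological parameters". A senior spine surgeon verifies a random selection.
- **Timing.** On the radiological and patient-related outcomes the section says: "These parameters will be measured at every follow-up moment (Table 1".
- **Safety.** The same section rests safety on (serious) adverse events together with complication rates. Adverse Events adds prospective capture, from patients' reports and from what the investigator and staff observe: "All AEs will be recorded throughout the study".
- **Relevance to the construct.** Proposed Surgical Technique explains that "2 transverse process hooks are placed at the upper-level vertebra to prevent proximal junction kyphosis".

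**The concern.** Proximal junctional kyphosis is defined by what a film shows. The trial measures the relevant angle repeatedly, with a trained reader and a verification step, yet the source named for it as a complication is the medical record. The angle itself is filed under sagittal balance.

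Whether a case enters the complication rate then depends on someone having recognised it and written it down, and that may vary between patients and visits. Safety is one of the two aims, and part of the construct is there specifically to prevent this complication. All patients come from one surgeon's practice and there is no control group, so the complication rate has no internal comparator against which incomplete detection would show.

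**Working it through.** **1. Sources side by side**

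| Source | What it captures | What must happen for a case to count |
|---|---|---|
| Medical record | Named source for proximal junctional kyphosis | It was recognised and entered in the record |
| Adverse event log | Any undesirable experience of the patient | The patient reports it, or the investigator or staff observe it |
| Measured junctional angles | A value at each follow-up with films | Nothing further, but no sentence turns the value into a complication |

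The first two sources need a person to notice and note the event. The third does not, and it is the one without a stated link to the complication rate.

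**2. Weight of one case**

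The plan gives no junctional kyphosis rate, so there is no figure of its own to reproduce. The denominator comes from Sample Size: 14 patients to be included, 12 needed for the analysis.

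- Change in rate per missed case = 1/n.
- n = 14: 1/14 = 7.1 percentage points.
- n = 12: 1/12 = 8.3 percentage points.

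**3. Illustration under assumed values**

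The true risk p and the detection probability s (chart and adverse event log combined) are assumptions; neither is in the documents. Expected recorded cases = 14 × p × s. Chance of recording at least one = 1 − (1 − p × s)^14.

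| p | s = 1.0 | s = 0.8 | s = 0.5 |
|---|---|---|---|
| 10% | 1.4 cases; 0.771 | 1.1; 0.689 | 0.7; 0.512 |
| 20% | 2.8; 0.956 | 2.2; 0.913 | 1.4; 0.771 |
| 30% | 4.2; 0.993 | 3.4; 0.979 | 2.1; 0.897 |

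Worked cell: p = 20%, s = 0.5 gives 14 × 0.2 × 0.5 = 1.4 cases and 1 − 0.9^14 = 0.771. At p = 20%, halving detection raises the chance of reporting no case at all from 0.044 (1 − 0.956) to 0.229 (1 − 0.771).

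**4. One assumed outcome**

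If 3 of 14 patients met an angle criterion and 1 had been noted, the report would read 1/14 = 7.1% (exact Clopper-Pearson 95% interval 0.2 to 33.9%) instead of 3/14 = 21.4% (4.7 to 50.8%). The intervals overlap widely. The example shows how sensitive a 14-patient rate is to single cases; it is not evidence that cases will be missed.

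**The case against.** The strongest reply has four parts.

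- **The chart is not the only source.** The complication list stands in a sentence meant to describe the patient group. The safety rule comes later and brings in prospective adverse event recording. This stands: a reader might infer that a case counts only if it was charted, and the text does not say so. It does not close the gap, because a symptom-free change in angle need not be reported by the patient, and no sentence makes a measured angle an adverse event.
- **The films may belong to the record.** Table 1 is a scheme of clinical care and includes the x-rays, so extraction from the record could include looking at the images. This also stands as a possibility. Even so, the article does not say that the measured angle decides the classification.
- **Operational detail may sit elsewhere.** A threshold, a derived variable and the reconciliation of sources may be in the full protocol or an analysis plan. Their absence from an article is not an error and is not counted as one here. What remains is that the article does name a source, and a more uniform one is already being collected.
- **No direction or size is documented.** A reader might conclude that the safety count is likely too low or favours the device. The documents give neither a junctional kyphosis rate nor a detection probability, so only the possibility of missed cases is supported.

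A reader might also extend the point to implant failure, which is in the same list. The junctional angles do not measure implant failure and no reading of implant integrity is among the listed parameters, so this contrast does not apply to it.

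**Conclusion.** The point holds for junctional kyphosis. The article assigns proximal junctional kyphosis to the medical record while the angles that would classify it uniformly are measured at every follow-up and left unconnected to the complication rate. The adverse event log is a genuine second source but shares the dependence on someone reporting or noting the event, so symptom-free radiographic cases may be missed.

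The size cannot be derived from the documents. What can be said is that each missed case moves the rate by 7.1 percentage points with 14 patients. The conclusion assumes that no document outside the article already makes the measured angle the basis for classification. It is a worthwhile improvement to a stated data source, not a flaw that invalidates the safety aim.

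**What to change.** In Data Collection and Statistical Analyses, state that proximal and distal junctional kyphosis are classified from the measured junctional angles by one criterion for change from the first postoperative film. Fix the criterion before the films are read, and apply it to every patient and every visit with films. Keep the medical record and the adverse event log as supplementary sources, and report one reconciled complication count that shows which source identified each case.

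This needs no extra visit, film or patient. The cost is one derived variable, a few sentences of text and some reconciliation work. The downside for the sponsor is that the reported complication rate may be higher.

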### Sample Size

To perform a sample size analysis, we compared our study to the study conducted by Miladi et al [23]. The sample size calculation is based on an ANOVA analysis and calculated using the statistical program G*Power (Heinrich-Heine-Universität Düsseldorf) [24,25].

Miladi et al [23] reported the results from the precursor of our OWSER system from the higher thoracic spine to the pelvis in 100 patients with NMS. The mean Cobb angle improved from 89° (range, 25°-149°) to 35° (range, 6°-53°) 3 years after surgery [23]. No SDs were reported. In light of this study, we expect a Cobb angle of 35° at maturity. To use these numbers for the sample size calculation, we assumed a normal distribution of the data; as such, the SDs of the preoperative Cobb angle were 31 and 11.75 for the postoperative Cobb angle [26]. We assumed a correlation of 0.5 and an effect size of 0.4 based on the correction described by Miladi et al [23]. The sample size calculation indicated that 12 patients ought to be included to examine the significant difference between the preoperative Cobb angle and the Cobb angle at the latest follow-up (power: 80%, significance level: 0.05).

Additionally, 20% more patients were included to account for a possible loss of subjects in the follow-up. In conclusion, the highest sample size indicated was 12; therefore, the minimal sample size needed for this study to address the primary goal is 14 patients. After the inclusion is completed, a post hoc power analysis will be performed to conclude if a significant number of patients is included in the study.

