## Discussion

### Principal Findings

Currently, all patients with AIS and diagnosed with curves exceeding 40° to 45° are recommended surgical correction followed by PSF to fix the patients’ spine for the rest of their lives [2,3]. In this study protocol, we describe a protocol to investigate the safety and efficacy of a minimally invasive posterior bipolar nonfusion OWSER for the surgical treatment of patients diagnosed with AIS.

The concept of PSnF for scoliosis surgery is not new. For patients diagnosed with EOS and NMS, multiple successful PSnF options are available and are currently regarded as the standard surgical treatment [16]. However, to the best of our knowledge, this concept has not been used in patients diagnosed with AIS.

The aim of this prospective study is to determine the efficiency and safety of the implant by analyzing radiological parameters (primarily Cobb angle), patient satisfaction scores, and complication rates. The expected primary benefit of this surgical technique is an efficient surgical correction of the Cobb angle without PSF. Because of the minimally invasive character of the surgical procedure, the spinal structures of the apex of the curvature between the thoracic and lumbar anchor points are not altered. Although some cases of auto-fusion have been described when using minimally invasive surgery [14], to the best of our knowledge, no complete full spinal fusion will occur. This might only allow the removal of the nonfusion OWSER at the end of spinal growth in patients in which the curve remains stable for a longer period of time and remains under 30° [27]. In addition, the system allows for a natural correction of the spinal deformity while the correct balance and alignment of the spine are maintained. Because of its self-expanding function, the system allows the patient to follow its final natural growth while functioning as an “internal brace.” Finally, due to the minimally invasive nature of the surgical procedure, the overall surgical time and general anesthesia time will be reduced, and the scar length can be limited to two scars that are 5-10 cm in length at the thoracic and lumbar fixation level.

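### The primary Cobb-angle ANOVA names no contrast, and a three-point omnibus test can be significant from the operative correction alone even if all of it is later lost

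*Protocol article*

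**What the plan says.** All references are to the protocol article.

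- **Comparison.** In Data Collection and Statistical Analyses, efficacy is the correction of the curve, "measured by comparing the preoperative and postoperative Cobb angle with the Cobb angle 2 years after maturity". Three time points are involved, and the final one is the comparator for the other two.
- **Test.** The same section states: "Differences between the Cobb angles and growth will be analyzed using repeated ANOVA measures". A mixed-model regression is added to adjust for age at surgery, Risser sign, weight and sex. Neither sentence names a contrast, a direction, a minimum correction or a tolerable loss.
- **Threshold.** A P "value of <.05 will be regarded as statistically significant".
- **Sample size.** The Sample Size section uses an ANOVA calculation in G*Power with effect size 0.4, correlation 0.5 and "power: 80%, significance level: 0.05". It arrives at 12 patients, raised to 14 for loss to follow-up. The text says the 12 are for the difference between the preoperative angle and the angle at last follow-up. It does not give the number of measurements entered.
- **Second operations.** These are listed among the patient characteristics: "when applicable, secondary surgery (including the time between the first and second surgery) will be extracted" from the medical record. The article does not say how a Cobb angle measured after one is used.

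**The concern.** The primary comparison contains two questions with opposite desired answers. Preoperative versus final should differ, because the curve was corrected. Postoperative versus final should differ little, because the correction was kept. A three-point repeated-measures ANOVA tests whether all three means are equal, and that hypothesis is false as soon as surgery straightens the curve. The article's section on the surgical technique says the initial correction comes from intraoperative traction, with concave distraction added. A significant omnibus F may therefore show only that the operation changed the first postoperative film.

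What is at stake is durability. The abstract's conclusions present the technique as one that "prevents the progression of the scoliotic curve", and the primary time point is 2 years after maturity. There is no control group, so this within-patient analysis carries the whole efficacy claim.

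The reverse error is also open. A non-significant postoperative-versus-final difference in 12 patients would be weak evidence that the correction was maintained.

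**Working it through.** **1. Reproducing the planned 12.** For a one-group repeated-measures ANOVA with m measurements, the noncentrality is λ = f²·n·m/(1−ρ), with df m−1 and (n−1)(m−1). Inputs from Sample Size: f = 0.4, ρ = 0.5, α = 0.05, power 80%. The article does not state m, so several values were tried.

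| m | λ at n = 12 | df at n = 12 | power at 12 | smallest n for 80% |
|---|---|---|---|---|
| 2 | 0.16·12·2/0.5 = 7.68 | 1, 11 | 71.4% | 15 (82.1%) |
| 3 | 0.16·12·3/0.5 = 11.52 | 2, 22 | 81.6% | 12 (81.6%) |
| 4 | 0.16·12·4/0.5 = 15.36 | 3, 33 | 88.7% | 10 (80.6%) |

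Only m = 3 gives exactly 12. The contrast that the text names is a two-measurement comparison. At n = 14 its power is 79.0% (λ = 0.16·14·2/0.5 = 8.96).

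**2. All correction lost, on the article's figures.** The means are 89°/35°/89° with SDs 31/11.75/31, ρ = 0.5 and n = 12, in 20,000 simulated trials. The 35° and its SD describe the reference series at 3 years and stand in here for the early postoperative film. The final values are set equal to the preoperative ones.
- Omnibus F significant: 100%.
- Direct preoperative-versus-final paired test: 5%, its nominal error rate.

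**3. All correction lost, at the planned effect size.** For means (d, 0, d) in SD units, f = d·√2/3, so f = 0.4 gives d = 0.849. For retained correction, the means (d, 0, 0) have the same f. Simulated at n = 12 (100,000 trials):
- All correction lost: omnibus 81.4%, direct contrast 5.0%.
- Correction fully kept: omnibus 81.6%, direct contrast 76.4%.

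The omnibus F cannot tell the two apart.

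**4. Assumed smaller curves.** Take 45°/(45−c)°/45° with a common SD and ρ = 0.5. Then f² = 2c²/(9·SD²), and at n = 12, m = 3, λ = 16c²/SD².

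| initial correction c | λ at SD 10 | omnibus at SD 10 | range, SD 12 to SD 8 |
|---|---|---|---|
| 5° | 4 | 37% | 27% to 55% |
| 10° | 16 | 93% | 80% to 99% |
| 15° | 36 | over 99% | 99% to 100% |

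The direct contrast stays at about 5% throughout. A Greenhouse-Geisser correction lowers the omnibus rates by at most about 4 percentage points.

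**5. Maintenance.** The paired-test power to detect a 5° loss (an illustrative size) at n = 12 is 75%, 51% and 35% for SDs of change of 6°, 8° and 10°.

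**6. Power of the direct contrast on the 89° to 35° figures.** The SD of the difference is √(31² + 11.75² − 2·0.5·31·11.75) = √734.8 = 27.1, so dz = 54/27.1 = 1.99. Five patients already give 90.7%.

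**7. Second operations (assumed scenario).** Two of 12 patients, each 30° lower after re-operation, move the final mean by 2·30/12 = 5°. In a second scenario every patient loses the implant's correction (45° curve, SD 10, n = 12) and some are re-operated to 20°. The direct contrast then shows significant improvement in 23% of trials if a quarter are re-operated and in 69% if half are.

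**The case against.** **The article never declares the omnibus F to be the efficacy criterion.** It makes the final angle the comparator, and Sample Size names preoperative versus last follow-up. With two levels, a repeated-measures ANOVA is the paired test, and contrasts are often left to an analysis plan, which is not shown here. This stands in part: a reader might infer that the plan has adopted the omnibus test as its pass rule, and the text does not say so. What remains is a mismatch inside the article. The printed test and threshold are tied to no contrast, and the planned 12 reproduces exactly only for three measurements. That number is inferred, because the article does not state it.

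**The second-operation part rests on silence.** A reader might infer that angles after re-operation will be credited to the implant. The article does not say that. It records second operations, their timing and implant failures, so they should be visible, and the full protocol may hold a rule. This is therefore a secondary point.

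**Rod removal is not a route to masked failure.** The Discussion's remark "This might only allow the removal of the nonfusion OWSER at the end of spinal growth" goes on to limit removal to curves that have stayed stable and below 30°. It does not support a claim that failures are hidden by removal.

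**The false signal is not certain.** With a 5° initial correction it is about 37% at SD 10. The 45° curve, its SDs and the re-operation shares are assumptions.

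**The 5° in the abstract is not a margin for lost correction.** It is an entry criterion for progression within one year before surgery, so it is used above only to illustrate power.

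**Conclusion.** The concern holds in this form: the primary ANOVA is not tied to the question the study asks, and the planned 12 fits a three-measurement omnibus test rather than the preoperative-versus-final comparison it is said to serve. If the omnibus F were read as evidence of lasting correction, it would be significant with all correction lost in 100% of trials on the article's figures. At SD 10 and n = 12 the rate is about 37%, 93% and over 99% for initial corrections of 5°, 10° and 15°. The direct contrast gives 5%.

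These rates assume normal data and a correlation of 0.5 between all time points. The result on the article's figures also uses the 3-year angle of the reference series as the early postoperative value. The documents support saying that the test can mislead. They do not show that it will, or that the investigators intend to rely on it.

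**What to change.** 1. **Data Collection and Statistical Analyses.** Make the mean change in main Cobb angle from preoperative to 2 years after maturity, with its 95% CI, the single primary contrast.
2. **Same section.** Report the change from postoperative to 2 years after maturity as an estimate with a 95% CI. State that maintenance is not inferred from P>.05 and that the omnibus F is not evidence of lasting correction.
3. **Sample Size.** Restate the calculation for that contrast, including the number of measurements. At effect size 0.4 and correlation 0.5, power is 71.4% with 12 patients and 79.0% with 14, and 15 evaluable patients are needed for 80%. If the article's 89° to 35° is used as the basis instead, power is ample; the text should say which basis applies.
4. **Secondary point.** Report how many patients had a second operation, and repeat the primary contrast leaving out Cobb angles measured after one. Leaving these out also removes patients who may have done badly, so this belongs beside the main result and the count, not in place of them.

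The cost is a change of wording with no new data, a stricter efficacy criterion and a slightly lower stated power. The article reports 5 patients included by October 2023, well before any of the planned 14 could all reach the primary time point, so the change can still be made in advance of the final data.
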